##### Promoting trans-sectional care—the SOFIA handbook

Owing to the Danish organization of health care and social care into different sectors resorting under separate laws, formal trans-sectional care plans are not feasible. However, each general practitioner assigned to the intervention arm will receive a specialized handbook, specific for their municipality and regional affiliation, containing contact information of relevant social or health care actors, and helplines in case of substance abuse and an increased risk of suicide and self-harm.

##### MMQ part 1

Apart from improving physical health, the SOFIA study aims to improve the quality of life among the participants. To measure the quality of life, we use the patient-related outcome measure, MMQ. MMQ was developed for patients with multimorbidity, including SMI. In the SOFIA pilot trial, we want to examine if the simultaneous use of MMQ as a conversation tool and an outcome assessment will bias the MMQ as an outcome measure. Therefore, the general practices will be cluster-randomized in two subgroups, with 2 general practices from each region in both subgroups. All patients are asked to complete the MMQ part 1 (MMQ1) before the prolonged consultation. In the first subgroup, the relative sum-scores of six scales will be provided to the general practitioners via an electronic link. During the educational course, the general practitioners in the first subgroup are instructed on how to use the six scales’ sum-scores as a clinical conversation aid during the “patient part” of the consultation. In the other subgroup, the general practitioners will not have access to the MMQ1 scores.

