#### Secondary outcome measures

To examine whether our recruitment strategy is at risk for preferential inclusion of patients with a favorable prognosis

To assess if, and to what extent, selective recruitment is present in our study, we aim to use national patient registries and registrations in REDCap to examine potential differences in demographic, socio-economic, and health-related characteristics between eligible patients who agreed and who declined participation in our study.
2.To examine to which extent use of the quality of life questionnaire (MMQ1) during the prolonged consultations threatens the validity of the questionnaire as an outcome measure

It is the intention, in the definitive trial, that the general practitioners can use the MMQ1 as a conversation tool to help them identify issues that should be addressed during the consultation. In this scenario, in the intervention arm, the general practitioners have access to the aggregated patients’ MMQ scores, and patients might have a different understanding of the questions after having discussed them during the consultation as opposed to the participants in the control group. This might compromise the validity of the MMQ1 as a primary outcome in the definitive trial. Within the pilot study, we aim to empirically test for this risk of bias. To this end, in randomly selected 50% of the intervention practices, the general practitioner will have access to the aggregated score of selected domains in the MMQ1. In the remaining 50% of the intervention practices, MMQ1 scores will be concealed for the general practitioner. This sub-study is designed as a small equivalence trial nested in the pilot study. The aim is to show that the two approaches are not different in terms of mean change in MMQ1 scores before and after the intervention by using the scores of MMQ2 and EQ-5D-5L as anchors.
3.To assess and inform selected aspects of program theory relating to the prolonged consultations and the educational course

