### Allocation and concealment

Unit of randomization will be the general practice so that all participating patients within the general practice receive either the intervention or care-as-usual. General practices will be randomly assigned on a 2:1 basis to either the intervention or care-as-usual group in blocks of three within each region. A block of three practices will be allocated simultaneously after completion of the baseline documentation for all study participants within the practices. Within each randomization block of 3 practices, we further randomize 1 of the 2 practices in the intervention arm to a sub-group, where the general practitioner has access to the aggregated scores of the MMQ1. The other intervention practice within the randomization block of 3, will be allocated to a sub-group in which MMQ1 scores will be concealed for the general practitioner. A computer randomized allocation sequence will be concealed until all general practices are assigned. Patients will be informed that they are allocated to the intervention arm or the control group by the research team through e-Boks.

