##### MMQ

The validated version of the MultiMorbidity Questionnaire (MMQ) encompasses two parts: MMQ1 and MMQ2. MMQ1 measures needs-based quality of life and MMQ2 measures self-perceived social inequity. MMQ1 encompasses 6 scales measuring: Physical ability (6 items); Worries (6 items); Limitations in everyday life (10 items); My social life (6 items), Self-Image (6 items); and Personal economy (3 items). The development of the items and the scales is based on the needs-based model for quality of life. MMQ2 encompasses different numbers of scales, with different numbers of items, that measure different constructs of self-perceived social inequity addressed towards five different types of contacts: general practitioners, the clinical staff at the general practice, other health professionals, the municipality employees, and finally, family, friends, and acquaintances.

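### The MMQ1-access sub-study is framed as an equivalence trial, but 4 versus 4 practices can support only an exploratory estimate, and equal mean change would not by itself show that MMQ1 is unbiased

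*Protocol article*

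**What the plan says.** Under Secondary outcome measures, item 2, the Protocol article explains that general practitioners are meant to use MMQ1 as a conversation tool in the definitive trial. It fears that patients who have discussed the questions may then understand them differently. Of the comparison that tests this it says "This sub-study is designed as a small equivalence trial nested in the pilot study". It then gives the purpose: "The aim is to show that the two approaches are not different in terms of mean change in MMQ1 scores". The change meant is from baseline to the end of the study, and the protocol would make the comparison "by using the scores of MMQ2 and EQ-5D-5L as anchors". The section MMQ part 1 puts the question as whether "simultaneous use of MMQ as a conversation tool and an outcome assessment will bias the MMQ as an outcome measure".

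The size follows from the allocation. Practices are "randomly assigned on a 2:1 basis to either the intervention or care-as-usual group in blocks of three within each region"; within each block, "we further randomize 1 of the 2 practices in the intervention arm to a sub-group" with access to the scores. MMQ part 1 gives the same layout: "with 2 general practices from each region in both subgroups". Power analysis and sample size caps recruitment at 15 patients per practice, gives no formal calculation, and justifies the number by the practicalities of delivery and data collection. Statistical methods names descriptive statistics and linear or logistic regression.

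**The concern.** Equivalence is a confirmatory claim: the confidence interval for the difference must lie inside a pre-set range. The protocol attaches that claim to a sample chosen for feasibility. With four practices a side the interval is likely to be too wide to exclude a distortion of moderate size, and if the aim were then judged by a difference test, a non-significant result would carry little information.

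There is a second difficulty. Access to MMQ1 is intended to improve the consultation, so it may truly improve quality of life. It may also change how patients answer. Mean MMQ1 change contains both effects. What is at stake is the soundness of the protocol's own empirical check on a questionnaire that is planned as a primary endpoint of the definitive trial.

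**Working it through.** **Size, from the protocol.** 12 practices in blocks of three give 4 blocks. Each block has 2 intervention practices, so 8 in all, one of each pair with access: 4 versus 4. At 15 patients each that is 4 × 15 = 60 per sub-group. The stated total reproduces (12 × 15 = 180). The protocol gives no figure for the sub-study's precision or power.

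**Assumptions, none of them in the protocol.** SD of change = 1; 15 patients per practice; complete data; ICC 0.01, 0.05 or 0.10; two one-sided tests at 5% each; true difference zero; practice-level analysis with 8 − 2 = 6 degrees of freedom.

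**Formulas.** SE = √(2 × (1 + 14 × ICC) / 60). The 90% half-width is 1.943 × SE, where 1.943 is the 95th percentile of t on 6 degrees of freedom. Equivalence power is by simulation. The last column is the chance that a two-sided 5% t-test is non-significant when the true difference is 0.5 SD (non-central t).

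| ICC | SE | 90% half-width (SD) | Power, margin 0.3 SD | Power, margin 0.5 SD | Margin for 80% power (SD) | True 0.5 SD difference missed |
|---|---|---|---|---|---|---|
| 0.01 | 0.195 | 0.38 | 7% | 49% | 0.65 | 43% |
| 0.05 | 0.238 | 0.46 | 2% | 26% | 0.79 | 58% |
| 0.10 | 0.283 | 0.55 | 1% | 13% | 0.94 | 68% |

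For a true 0.3 SD difference the miss rate is 74 to 85%.

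**Sensitivity.**
- ICC 0: power is 9% at 0.3 SD and 57% at 0.5 SD; the 80% margin is 0.61 SD.
- 90% response (0.9 × 15 = 13.5 per practice) at ICC 0.05: 2% and 23%.
- Analysis within the four blocks (3 degrees of freedom): the 80% margin becomes 0.75 to 1.09 SD for ICC 0.01 to 0.10.
- Adjusting for baseline instead of using raw change multiplies the variance by (1 + ρ)/2, that is 0.75 to 0.85 for an assumed pre-post correlation ρ of 0.5 to 0.7. At ICC 0.01 the SE falls to 0.195 × √0.75 = 0.169 or 0.195 × √0.85 = 0.180, and power at 0.5 SD rises to 59 to 67%. At 0.3 SD it is still only 10 to 13%.

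**Size that would be needed.** For 80% power at a 0.3 SD margin, n per sub-group = 2 × ((1.645 + 1.282)/0.3)² ≈ 191. Multiplying by (1 + 14 × ICC) and dividing by 15 gives 15, 22 and 31 practices per sub-group at the three ICCs. At 0.5 SD, n ≈ 69, which gives 6, 8 and 12 practices (a normal approximation, so slightly too few).

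**What the contrast identifies.** Write the expected difference in MMQ1 change as B + S, with B the real benefit of access and S the change in how questions are answered. If B = 0.3 and S = −0.3, the means are equal and the measure is biased. If B = 0.3 and S = 0, the means differ and the measure is sound. The anchors are the protocol's means of separating B from S, but each is partial:
- MMQ2 covers "self-perceived social inequity addressed towards five different types of contacts: general practitioners, the clinical staff at the general practice" and three further types outside the practice. The aid may change the conduct of the first two, so MMQ2 may itself respond to access. It also belongs to the questionnaire under test.
- EQ-5D-5L covers five health-status dimensions and has none for the MMQ1 scales on self-image or personal economy.

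**The case against.** The strongest reply is that this is a secondary objective of a pilot, called small by its authors and introduced as examining an extent. A pilot needs no power calculation, and a margin, an equivalence test and anchor rules may sit in an analysis plan that is not shown. All of that stands: neither the missing margin nor the missing calculation is the fault here. What remains is that the protocol itself sets an aim of showing no difference, and no later analysis plan can turn 4 versus 4 practices into more.

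The power figures also rest on assumed values. At a 0.5 SD margin with a low ICC they are about even, and better with baseline adjustment. A reader might infer from the table that an inconclusive result is near certain; that fits a margin near 0.3 SD, not every plausible margin.

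A reader might also infer that the result decides whether general practitioners may see MMQ1 scores in the definitive trial. The protocol does not say so. Such use is already its intention, progression decisions are tied to objectives with thresholds, and this objective has none. Nor does any section say that a non-significant test will be read as equivalence; the miss rates show what would follow if it were.

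Finally, MMQ2 should not be described as a measure of treatment by the practice. It measures perceived social inequity across five contact types, three of them outside the practice. The doubt about it as an anchor is therefore partial, and there is no good ground for making EQ-5D-5L the only anchor.

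**Conclusion.** The concern holds in limited form. The equivalence wording claims more than the fixed design can deliver. For ICCs of 0.01 to 0.10, 15 patients per practice and complete data, equivalence could be shown with 80% power only within 0.65 to 0.94 SD of the change score. ICC, SD and margins are assumptions, but the conclusion for a 0.3 SD margin does not depend on them closely: even at ICC 0 power is 9%. Separately, equal mean change would not establish that MMQ1 is unbiased, and the two anchors reduce that ambiguity without removing it.

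It would be tempting to rate this as a defect that must be repaired before the trial can proceed. The protocol does not support that rating: the objective is secondary and no decision rule hangs on it. It is a lower-severity correction of a stated aim.

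**What to change.** In Secondary outcome measures, item 2:
- Replace the equivalence label and the aim of showing no difference with an exploratory aim of estimating how access to MMQ1 scores affects MMQ1.
- Report the access-minus-concealed difference in end-of-study MMQ1, adjusted for the pre-randomisation score, with a practice-level (cluster-adjusted) 90% confidence interval on at most 6 degrees of freedom.
- State that a non-significant difference will not be taken as absence of bias.
- Describe the relation of MMQ1 to each anchor by sub-group without drawing an equivalence conclusion, and also report MMQ2 as an outcome that access may affect.

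The cost is a less favourable claim. Randomisation, recruitment and data collection stay as they are. Keeping the equivalence claim would instead require a justified margin and more practices, on the scale shown in the working.

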### Power analysis and sample size

As this is a pilot trial, a formal sample size calculation is not performed. We aim to include 12 practices, each recruiting up to 15 patients per practice, amounting up to 180 patients in total. We considered this number sufficiently informative on the practicalities of delivering the intervention and collecting outcome data.

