### Statistical methods

The quantitative parts of the primary objectives in this pilot study, e.g., the rate of recruitment of general practitioners and patients, retention of patients, and outcome data, will primarily contain descriptive statistics to assess the quality of these parameters: Mean (standard deviation) for continuously measured objectives, and raw count (%) for categorically measured objectives. For some objectives, the difference between the randomization groups is of interest, and this will be assessed statistically in linear or logistic regression models.

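### The nested MMQ1 equivalence comparison is defined as mean change, and the article does not say that it adjusts for the baseline MMQ1 score already collected

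*Protocol article*

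**What the plan says.** Under Secondary outcome measures, the second objective asks whether using MMQ1 in the consultation undermines it as an outcome. The article states: "This sub-study is designed as a small equivalence trial nested in the pilot study". The quantity to be compared between the score-shown and score-concealed practices is the "mean change in MMQ1 scores before and after the intervention", with MMQ2 and EQ-5D-5L serving as anchors.

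Under Allocation and concealment: "General practices will be randomly assigned on a 2:1 basis to either the intervention or care-as-usual group in blocks of three within each region". The split for the sub-study follows: "Within each randomization block of 3 practices, we further randomize 1 of the 2 practices in the intervention arm to a sub-group". The section MMQ part 1 agrees, with two practices per region in each sub-group.

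The only statement about a model is in Statistical methods: "For some objectives, the difference between the randomization groups is of interest, and this will be assessed statistically in linear or logistic regression models". It lists no covariates.

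Two other places bear on the point. Quality of life measurements, under Data collection before randomization, has MMQ and EQ-5D-5L collected from every recruited participant ahead of allocation. The Discussion accepts that cluster randomization can leave the arms unlike each other, and calls for correction in the analysis of the definitive trial. It says nothing of the kind for the pilot or its sub-study.

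**The concern.** Read at face value, the baseline score enters the comparison only through subtraction. Subtraction gives baseline a coefficient of 1, whereas the best linear predictor, with equal standard deviations at both times, gives it a coefficient of rho. When rho is below 1, the change score over-corrects: a group that happens to start lower shows a larger mean gain through regression to the mean.

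Chance differences at baseline are plausible here. Each sub-group has four practices, and recruitment instructions require only two or more patients from each diagnostic group, so case mix can vary from practice to practice.

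Equivalence is judged from an interval around a difference. Avoidable width makes equivalence harder to show, and an uncorrected baseline difference can mimic or hide an effect of showing the scores. No formal sample size calculation was made, so no planned precision is held in reserve. The result is meant to inform whether MMQ1 can serve both as a conversation tool and as an outcome in the definitive trial.

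**Working it through.** **1. Size, from the article.** Power analysis and sample size gives: "We aim to include 12 practices, each recruiting up to 15 patients per practice, amounting up to 180 patients in total". 12 × 15 = 180, which reproduces the stated total. With 2:1 allocation, 12 × 2/3 = 8 intervention practices. One of each pair is shown the scores, so 8/2 = 4 practices per sub-group and at most 4 × 15 = 60 patients per sub-group. The article gives no equivalence limits, standard deviation (SD), intracluster correlation (ICC) or rho, so the last two are varied below and results are in units of one patient SD.

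**2. Precision.** With equal SD s at both times:
- variance of change: 2s²(1−rho)
- residual variance after adjusting for baseline: s²(1−rho²)
- ratio: 2(1−rho)/(1−rho²) = 2/(1+rho)

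**3. Chance baseline difference.** Its SD is sqrt[(2/60)(1 + 14 × ICC)], which is 0.18 at ICC 0, 0.24 at ICC 0.05 and 0.28 at ICC 0.10. A baseline difference D moves the unadjusted change estimate by −(1−rho)D.

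**4. Results at ICC 0.05.** Standard errors (SE) use the design effect 1 + 14 × 0.05 = 1.70.

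| rho (assumed) | Variance ratio 2/(1+rho) | SE, change | SE, adjusted | Size of shift for a one-SD imbalance |
|---|---|---|---|---|
| 0.3 | 1.54 | 0.282 | 0.227 | 0.167 |
| 0.5 | 1.33 | 0.238 | 0.206 | 0.119 |
| 0.7 | 1.18 | 0.184 | 0.170 | 0.071 |
| 0.9 | 1.05 | 0.106 | 0.104 | 0.024 |

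**5. One effect, not two.** 2(1−rho) − (1−rho²) = (1−rho)². The extra variance is exactly the variance of the shift in step 3. At rho 0.5, 0.238² − 0.206² ≈ 0.014, and 0.119² ≈ 0.014.

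**6. Simulation check.** For each scenario, 4,000 trials of eight practices with 15 patients each were simulated at ICC 0.05 with no true difference.
- Both estimators averaged within 0.003 of zero, so neither is biased over randomizations.
- With the same correlation at practice and patient level, the slope of the change estimate on the baseline difference was −0.50 (rho 0.5) and −0.30 (rho 0.7). The adjusted estimate had slopes of about 0.
- With a practice-level correlation of 0.9, the slopes were −0.34 and −0.22 for change, against +0.14 and +0.08 for the adjusted estimate. The SDs of the estimates were 0.194 v 0.182 (rho 0.5) and 0.156 v 0.149 (rho 0.7). The variance excess is then (0.194/0.182)² = 1.14 and (0.156/0.149)² = 1.10, smaller than in the table.
- Regressing change on sub-group and baseline gave the same sub-group effect as regressing the end score on sub-group and baseline (largest difference about 2 × 10⁻¹⁵).

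**The case against.** The strongest reply is that the article names an outcome measure and not a model. A reader might infer that the plan commits to a raw, unadjusted comparison of change in place of a baseline-adjusted one. The documents do not support that. The article nowhere says the comparison is unadjusted, and its only model statement is that a group difference of interest, in its words, "this will be assessed statistically in linear or logistic regression models". A linear regression of change with baseline as covariate fits that statement and gives the same sub-group effect as adjusting the end score. Covariates are also commonly left to an analysis plan, and that plan is not shown. This reply stands against any charge of error. It does not remove the point that the article fixes change as the measure, mentions imbalance correction only for the later trial, and leaves unstated an adjustment that needs no new data.

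The second reply is that the objective concerns measurement validity, with MMQ2 and EQ-5D-5L as anchors, so a plain between-group difference in end score would answer another question. This stands as a limit on the remedy: the anchor comparisons must remain.

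The third reply is that the figures rest on assumed rho and ICC, that the gain is slight at high rho, and that the imbalance formula ignores the pairing of practices within regional blocks. All of this stands. With four practices against four, the number of practices limits precision more than the covariate does.

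**Conclusion.** The point holds as a free improvement of modest size. The sub-study comparison is defined as a difference in mean change without a statement that it adjusts for the pre-allocation MMQ1 score. If no baseline term is used, the variance is about 54% to 5% larger than it need be for rho 0.3 to 0.9 (33% at 0.5, 18% at 0.7), assuming equal SDs at both times and the same correlation at practice and patient level. If practice means are more stable over time than individual scores, the excess is smaller. At ICC 0.05, an imbalance of one SD (0.24) moves the estimate by 0.12 at rho 0.5 or 0.07 at rho 0.7.

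Three stronger readings should be resisted. The shift is not systematic bias: it depends on the imbalance that happens to occur and averages to zero over randomizations. The wider interval and the shift are not separate harms, as step 5 of the working shows. Nor does the sub-study decide whether practitioners may see MMQ1: the article sets out to examine the extent of the threat to validity and attaches no threshold to this objective. The point is also confined to the sub-study, since the article names no specific MMQ or EQ-5D-5L comparison between the main arms.

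**What to change.** Add one sentence to Secondary outcome measures (objective 2) or Statistical methods. It should say that the MMQ1 comparison uses a linear model of the end-of-study score, or of change, on sub-group, with the baseline MMQ1 score as covariate and region as the stratification factor, and that it accounts for clustering by practice. Specify the score taken before allocation as the baseline, because the participants' timeline also marks MMQ1 at allocation. Keep the MMQ2 and EQ-5D-5L anchor comparisons as planned.

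Mean change can still be reported descriptively. The cost is wording only: the baseline scores are already collected, and neither the design nor the data collection changes.
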